#### Secondary Outcomes

The secondary outcomes are as follows:

Cannabis use will be measured using a self-report tool, the Timeline Follow Back (TLFB) [57]. On the basis of the TLFB, for each day in the last 14 days, participants indicate first if they used cannabis (yes or no). To facilitate their recollection, participants will be asked about memorable days (eg, birthdays) and patterns of use (eg, more use on weekends). Then, for each day they used cannabis, they will provide the quantity of cannabis used. Participants will be reasked about the cannabis form used (dried cannabis smoked, oral spray, oral oil, dried cannabis vaporized, concentrated vapor, oral capsules, beverages, edibles, etc) and for each form, they will provide the quantity and the unit (eg, g, mg, and mL) and the concentration in tetrahydrocannabinol and cannabidiol (%, mg/mL, mg/dose, or unknown). The quantity of cannabis used on a specific day represents grams per method of cannabis use (eg, dried cannabis smoked) × number of times the method is used per day. The quantity of cannabis used in the last 14 days will be calculated. The inclusion of the quantity of cannabis use as a secondary outcome, which has been used in other similar trials [35], is justified by research suggesting that in individuals with psychosis and CUD, face-to-face psychological interventions (MI and CBT) are more effective in decreasing the quantity than the frequency of use [22].Participant satisfaction with using iCC or programs for CUD offered as part of EIS (control group) will be measured with the validated 8-item Client Satisfaction Questionnaire (CSQ-8) [58]. Items (eg, “How would you rate the quality of program you received”) are scored on a scale from 1 to 4 and a higher total score reflects higher satisfaction. Participants who discontinue participation in the study will be invited to complete the CSQ-8 upon discontinuation. Other details about their experiences are collected in an open-ended format.App use: Considering the importance of evaluating app use and adoption metrics in eHealth trials [43], data will be collected automatically through iCC for the entire 24-week participation in the intervention. The following outcomes will be monitored: number of iCC modules and strategies completed, number of times a particular module was opened and completed, time spent on individual iCC modules, time elapsed between the initiation and completion of individual iCC modules, and total time spent completing the iCC intervention and boosters. For each participant, iCC data will be synchronized with a password-protected Amazon Web Services account for a period of 24 weeks. Data related to clinicians’ use of the dashboard (ie, number of logins) are synchronized with the Amazon Web Services account and will be used for exploratory analyses of clinician involvement in monitoring participant progress during the intervention.Trial parameters: Information collected during enrollment and study visits (stored in REDCap) will allow us to calculate the number of participants who were referred to the study, screened, eligible, provided informed consent, randomized, initiated the intervention (ie, who both logged into iCC and complete module 1), and completed baseline and follow-up assessments.

#### Exploratory Outcomes

The exploratory outcomes are as follows:

Cannabis use frequency (and abstinence) will be measured using the TLFB. Participants who declare using alcohol will be asked about the frequency and quantity of use, and those who consume other substances (eg, cocaine, amphetamine, opioids) will be asked about the frequency of use and route of administration.Cannabis-related negative social, occupational, physical, and personal consequences will be assessed using the 19-item unidimensional self-report instrument, the Marijuana Problems Scale (MPS) [59,60]. Higher MPS scores (range 0-38) denote more negative cannabis use consequences.Cannabis use disorder severity will be measured with the 5-item Severity of Dependence Scale (SDS), which has been validated in people with early psychosis [61,62]. Higher total scores (range 0-15) indicate more severe dependence symptoms.Confidence in resisting cannabis use in 8 different situations (eg, “if other people treated me unfairly or interfered with my plans”) will be measured using the validated Drug-Taking Confidence Questionnaire (DTCQ) [63], with higher scores denoting higher confidence levels to resist cannabis use.The measurement of intentions to stop using cannabis has been informed by and adapted from the Precaution Adoption Process Model [64], a theoretical stage-based model that allows participants to place themselves in one of 6 nominal stages: (1) unengaged (ie, “As of right now, I haven’t thought about if I want to stop using cannabis”); (2) undecided (ie, “I’m still unsure if I want to stop”); (3) decided not to act (ie, “I do not want to stop”); (4) decided to act (ie, “I want to stop”); (5) acting (ie, “I recently stopped”); and (6) maintenance (ie, “I stopped using cannabis over a month ago”).The severity of positive and negative symptoms of psychosis will be measured using an interviewer-administered scale, the Positive and Negative Syndrome Scale (PANSS-6) [65]. This well-validated short version of the PANSS has been chosen rather than the complete 30-item version to reduce the burden of data collection. A total score of 6 reveals no psychotic symptoms, and a total score of <14 will be considered the cutoff for remission of schizophrenia [65].To measure cannabis-related harm, we will use the 17-item Protective Behavioral Strategies-Marijuana (PBSM) questionnaire, which has been shown to be valid and free of bias in terms of gender, sex, race, ethnicity, and recreational marijuana use legal status [66]. We use the table provided by Pedersen et al [66] to convert the sum score into Item Response Theory scale scores, with higher scores indicating higher-risk behaviors [66].Participants will report their Satisfaction with Life pertaining to 4 domains (ie, living situation, social relationships, work, self, and present life) using the 18-item Satisfaction with Life questionnaire (SWL), which has been validated for schizophrenia and schizophrenia-related disorders [67]. In each domain, higher mean scores indicate greater satisfaction.Self-reported health service use data using the Health Care form will include emergency department visits and hospitalizations for psychological, emotional, or mental health issues in the last 30 days (yes or no). In the case of hospitalization, additional data will be collected (ie, number of admissions, duration of stay, reason for admission, and confirmation using medical records).

### Sample Size

Sample size calculations were guided by the results of studies that used psychological app-based interventions targeting cannabis use in individuals without psychosis [68] or with subthreshold psychosis [38], in which attrition was lower than 33% and the intervention completion rate was approximately 50%. We will use a CI approach with binomial SEs and normal approximation [69] to calculate the number of participants needed to reject the null hypothesis that at 12 weeks, the attrition will be ≥50% (expected maximum attrition of 30%) and intervention completion will be ≤50% (the minimum expected proportion of participants who download the app and complete at least 11 out of 21 intervention modules—excluding the 3 boosters—is 70%). We calculated that at least 33 participants must be randomized per study arm to maintain 80% power to detect hypothesized effects with a 1-sided significance level of 5%. For the intervention completion outcome, we adjusted the sample size for an estimated 30% attrition and calculated that a total of approximately 100 participants will be needed for this study (2 × 33 / 0.7 = 94).

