**Methods:**

Consenting individuals (n=100) meeting the inclusion criteria (eg, aged 18-35 years with FEP and CUD) will be randomly allocated in a 1:1 ratio to the intervention (iCC+modified EIS) or control (EIS) group. The iCC is fully automatized and contains 21 modules that are completed over a 12-week period and 3 booster modules available during the 3-month follow-up period. Validated self-report measures will be taken via in-person assessments at baseline and at 6, 12 (end point), and 24 weeks (end of trial); iCC use data will be collected directly from the mobile app. Primary outcomes are intervention completion and trial retention rates, and secondary outcomes are cannabis use quantity, participant satisfaction, app use, and trial recruiting parameters. Exploratory outcomes include severity of psychotic symptoms and CUD severity. For primary outcomes, we will use the chi-square test using data collected at week 12. We will consider participation in iCC acceptable if ≥50% of the participants complete at least 11 out of 21 intervention modules and the trial feasible if attrition does not reach 50%. We will use analysis of covariance and mixed-effects models for secondary outcomes and generalized estimating equation multivariable analyses for exploratory outcomes.

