### Statistical Analyses

The 1-sided chi-square 95% CI will be calculated to estimate the lower bound of iCC completion and trial retention rates. We will consider participation in iCC acceptable if more than 50% of the participants completed at least 11 out of 21 intervention modules at week 12. The trial will be considered feasible if the attrition at week 12 does not reach 50%. An analysis of covariance model will be used to provide a preliminary assessment of the effect of treatment on the quantity of cannabis use (dependent variable) at 12 weeks (end of intervention). The independent variables will be the quantity of cannabis use at baseline and a dichotomous variable reflecting arm allocation. The second model will include covariates that were found to be different between the groups at baseline. For participants’ satisfaction with the intervention, we will calculate the CSQ total scores as well as the mean and SD. The groups will be compared using a mixed-effects model with random intercepts for each site. For app use and trial parameters, we will use univariate analyses and report the distribution (frequency tables), central tendency (mean, median, and mode), and dispersion (range and SD).

For exploratory outcomes, we will compute descriptive statistics and bivariate and multivariable analyses using generalized estimating equation (GEE) models. The generalized estimating equation is a repeated-measures regression model that accounts for the correlations between repeated measures for each person [70]. We will use different types of GEE modeling depending on the distribution of the outcome. For cannabis frequency (count data), we will use Poisson; for the abstinence (binary), we will use binomial; and for continuous variables (ie, scores calculated for MPS, SDS, DTCQ, PANSS, PBSM, SWL, and SPS), we will use linear GEE modeling. Using this analytic approach, we will estimate the multivariable associations between the outcomes and study visits (ie, baseline and end of intervention), study condition (the reference group will be the control arm), and their interaction, as well as other predictors and covariates, such as sociodemographics, social support, CUD severity, behavioral stage of change, medication status, and other substance use. We will use the chi-square test of proportions to compare behavioral stages at different time points and between the 2 study arms.

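### The 80% power stated for 33 per arm is a normal-approximation figure; actual power at 33 is 73.3%, although the planned 47 to 50 per arm exceeds 80%

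*Protocol article*

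**What the plan says.** Sample Size in the protocol article sets out the method: "We will use a CI approach with binomial SEs and normal approximation [69] to calculate the number of participants needed". The null hypotheses are that "the attrition will be ≥50% (expected maximum attrition of 30"%) and that "intervention completion will be ≤50"%; the expected completion rate, "excluding the 3 boosters—is 70"%. Both primary outcomes therefore come down to a true rate of 70% (retention or completion) against a fixed 50%, "with a 1-sided significance level of 5"%. The result is stated as "We calculated that at least 33 participants must be randomized per study arm to maintain 80% power to detect hypothesized effects". For the completion outcome this is inflated for 30% attrition to 94 and rounded to about 100 in total.

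The analysis is described in other terms. Statistical Analyses says "The 1-sided chi-square 95% CI will be calculated to estimate the lower bound of iCC completion and trial retention rates", and the Methods paragraph of the Abstract says "For primary outcomes, we will use the chi-square test using data collected at week 12". The section on the primary outcomes sets the denominator for both outcomes as everyone randomised.

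**The concern.** A sentence that ties a sample size to a power should hold for the test that will be run. Here the sizing uses a confidence interval with binomial standard errors, while the analysis names a chi-square bound and does not say which standard error that bound uses. The 33 is also the base of the published total, and the article gives no power for the size actually planned. A reader who takes 33 per arm as a floor for 80% power, for example when a change in sample size is considered on the monitoring board's advice (Other Information), would be relying on a figure that 33 participants do not deliver.

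**Working it through.** **Inputs.** Null rate 0.50, true rate 0.70, one-sided 5% (z = 1.645), 80% power (z = 0.842), 33 per arm, 30% inflation, total 94 to about 100: all from Sample Size. Denominator of all randomised: from the primary outcomes section.

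**1. Reproduce the plan's figure.** One-sample Wald formula with the standard error at 70%:

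n = (1.645 + 0.842)² × 0.70 × 0.30 / 0.20² = 6.183 × 0.21 / 0.04 = 32.46, rounded up to 33.

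Nominal power at 33: Φ(0.20 / √(0.21/33) − 1.645) = 80.6%. Inflation: 2 × 33 / 0.7 = 94.3. The stated figures are reproduced.

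**2. Actual power at 33.** Find the smallest count that rejects 50%:

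| Count | Wald lower bound | Score z (needs > 1.645) | Exact one-sided p |
|---|---|---|---|
| 21/33 | 0.4986 | 1.567 | 0.081 |
| 22/33 | 0.5317 | 1.915 | 0.040 |

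All three rules fail at 21 and pass at 22. Actual one-sided error is P(X ≥ 22 | 33, 0.50) = 4.0%. Actual power is P(X ≥ 22 | 33, 0.70) = 73.3%.

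**3. The score form of a chi-square bound (an assumption).** With the null standard error in the critical value:

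n = (1.645 × 0.5 + 0.842 × √0.21)² / 0.20² = 36.49, so 37 per arm.

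Its normal-approximation power at 33 is Φ((0.20 − 1.645 × 0.5/√33) / √(0.21/33)) = 76.2%. At 37, all three rules need 24; actual error is 4.9% and actual power 80.7%.

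**4. The planned size, all randomised in the denominator, true rate 70%.**

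| n per arm | Rule | Passes at | Actual error | Actual power |
|---|---|---|---|---|
| 47 (94/2) | Wald | 29 | 7.2% | 91.7% |
| 47 | score, exact | 30 | 4.0% | 86.0% |
| 50 | Wald, score (uncorrected) | 31 | 5.95% | 91.5% |
| 50 | exact | 32 | 3.25% | 85.9% |

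Between these sizes the power moves in steps. The lowest value is for the exact test at 48 per arm, P(X ≥ 31 | 48, 0.70) = 83.6%, which is still above 80%.

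**5. Where the choice of rule matters.** At 33 the rules agree. At the planned sizes they do not: 29/47 passes under Wald only, and 31/50 passes under Wald or uncorrected score but not under the exact test. The rules that pass at 31/50 have an actual error above the stated 5%.

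**The case against.** The best reply is that nothing was miscalculated. The article declares a normal approximation, and by that method 33 is right, with 80.6% power. That stands: this is an approximate power quoted without qualification, not a slip in arithmetic.

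A second reply is that 33 is a low point of a sawtooth. With the uncorrected score rule, 34 gives 80.7% power (actual error 6.1%), 35 gives 77.3% (4.5%), and 38 falls to 77.5% although 37 gives 80.7%. That also stands. It means that merely replacing 33 by 37 would settle little, and that the power worth stating is the one for the planned size under a named test.

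Third, Statistical Analyses does not define the standard error of its chi-square interval, and such detail is commonly left to an analysis plan. So the figure of 37 is conditional on the score form.

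A reader might infer more than this. One inference is that the different descriptions of sizing and analysis cause the 73%. They do not: the Wald and score rules share the same cut-off at 33, and the change of formula alone lowers the approximate power only to 76.2%. Another is that the trial runs a 27% false-negative risk (100 − 73.3), or that the total should be 2 × 37 / 0.7 = 106. Neither describes this trial, because 33 is not the number to be analysed. About 47 to 50 per arm are to be randomised and all of them are counted.

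**Conclusion.** The sentence on 33 per arm is wrong as a statement of actual power: 73.3%, against the 80% claimed, under all three rules examined. The shortfall comes from the normal approximation and the discreteness of the binomial count. It is a minor point, because the design itself is adequate: about 86% to 92% at 47 and at 50 per arm. That conclusion rests on two assumptions: that the denominator is everyone randomised, as the primary outcomes section states, and that 70% is the true rate among everyone randomised. The documents do not support a claim that the trial is underpowered or needs more participants.

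**What to change.** Change the wording of Sample Size and Statistical Analyses:

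- State that 33 per arm gives 80% power only by the Wald normal approximation, and about 73% actual power.
- Name one test, and use it for both the sizing and the primary analysis.
- Report the power for the planned 50 per arm with all randomised in the denominator. With the exact one-sided binomial test this is 85.9% at a true 70%, requiring at least 32 of 50, with actual error 3.25%. If the uncorrected Wald or score rule is preferred, say that it passes at 31 of 50 with actual error 5.95%, above the stated 5%.

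The cost is a few sentences and one slightly less favourable figure for 33. Enrolment and the planned total are unchanged.

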### Randomization and Blinding

Once baseline assessments are completed, participants will be randomized to either (1) iCC+mEIS or (2) EIS. Within each stratum, based on biological sex, a random 1:1 group allocation sequence is generated using a permuted block design with blocks of varying sizes to decrease the likelihood of predictability of group assignment. The group allocation will not be masked, and the baseline visit concludes with participants logging into iCC and completing the introductory module. If a participant drops out of the study at any point following randomization, the randomization slot will not be reallocated to a new participant. The randomization schedule is concealed within the secure REDCap system and was created by the CHUM Center for the Integration and Analysis of Medical Data (CITADEL). The study participants, clinicians, and research staff conducting assessments will not be blinded to the group assignment, while individuals performing analyses will be blinded.

### Statistical Analyses

The 1-sided chi-square 95% CI will be calculated to estimate the lower bound of iCC completion and trial retention rates. We will consider participation in iCC acceptable if more than 50% of the participants completed at least 11 out of 21 intervention modules at week 12. The trial will be considered feasible if the attrition at week 12 does not reach 50%. An analysis of covariance model will be used to provide a preliminary assessment of the effect of treatment on the quantity of cannabis use (dependent variable) at 12 weeks (end of intervention). The independent variables will be the quantity of cannabis use at baseline and a dichotomous variable reflecting arm allocation. The second model will include covariates that were found to be different between the groups at baseline. For participants’ satisfaction with the intervention, we will calculate the CSQ total scores as well as the mean and SD. The groups will be compared using a mixed-effects model with random intercepts for each site. For app use and trial parameters, we will use univariate analyses and report the distribution (frequency tables), central tendency (mean, median, and mode), and dispersion (range and SD).

For exploratory outcomes, we will compute descriptive statistics and bivariate and multivariable analyses using generalized estimating equation (GEE) models. The generalized estimating equation is a repeated-measures regression model that accounts for the correlations between repeated measures for each person [70]. We will use different types of GEE modeling depending on the distribution of the outcome. For cannabis frequency (count data), we will use Poisson; for the abstinence (binary), we will use binomial; and for continuous variables (ie, scores calculated for MPS, SDS, DTCQ, PANSS, PBSM, SWL, and SPS), we will use linear GEE modeling. Using this analytic approach, we will estimate the multivariable associations between the outcomes and study visits (ie, baseline and end of intervention), study condition (the reference group will be the control arm), and their interaction, as well as other predictors and covariates, such as sociodemographics, social support, CUD severity, behavioral stage of change, medication status, and other substance use. We will use the chi-square test of proportions to compare behavioral stages at different time points and between the 2 study arms.

Missing entries for fields where missing values account for <5% of the sample may be imputed using the sample mean for continuous variables and sample mode for categorical variables. Fields with >5% missing entries may be excluded from multivariate models. In the case of missing visits, the proposed types of analyses (linear mixed-effects models and GEE models) will include all participants with at least one nonmissing visit, which may increase statistical power and reduce estimation bias. Our analysis plan includes both intention-to-treat and per-protocol analyses.

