To consider the trial feasible, at least 50% of participants must complete all study assessments at week 12, which corresponds to the end of the iCC main intervention (excluding booster sessions). In the absence of similar trials in our target population, we chose this cutoff conservatively, as it is close to the maximum attrition rate of 65% reported in studies using app-based interventions for decreasing cannabis use in individuals *without psychosis* [34-36]. Our approach is justified by the clinical characteristics of participants attributable to psychosis and CUD, which could represent a barrier in complying with the study procedures. However, we expect an attrition rate closer to 30% because we tailored the iCC intervention to participants’ needs, restricted inclusion criteria to participants interested in using an app-based psychological intervention, and planned to offer iCC to participants allocated to the control arm at the end of the study. In addition, the intensive clinical follow-up that is offered in EIS for psychosis could contribute to lower attrition rates. Other implemented strategies that could reduce loss to follow-up include maintaining an updated record of participant contact information throughout the study, scheduling study visits according to participant availability, and offering flexible in-person or web-based study visit assessments.

In individuals with psychosis, face-to-face psychological interventions were found to be more effective in decreasing the quantity than frequency of cannabis used [22]. However, no study has evaluated the effects of mHealth interventions on the quantity of cannabis used in individuals with CUD and psychosis. In their RCT that included a web-based psychological intervention in individuals without psychosis, Rooke et al [35]) found a small effect (Cohen *d*=0.19) of a short 6-module intervention on the quantity of cannabis consumed at the 12-week follow-up [35]. Similar to the intervention used by Rooke et al [35], iCC incorporates behavioral and motivational approaches tested by Copeland et al [47]. Our pilot study will offer valuable information related to using a higher-intensity 19-module intervention and offering support during clinical encounters to participants who have difficulties in completing iCC.

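### The trial is sized to reject 50% at a one-sided 5% level, but its acceptability and feasibility criteria compare the observed rate with 50% and are not tied to the planned lower bound

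*Protocol article*

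**What the plan says.** All references are to the protocol article.

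- **Sample Size** uses a confidence-interval approach to "calculate the number of participants needed to reject the null hypothesis that at 12 weeks, the attrition will be ≥50" per cent, with the mirror-image null for completion (50% or less). The expected rates are at most 30% attrition and at least 70% completion. The size and power are given as: "We calculated that at least 33 participants must be randomized per study arm to maintain 80% power". The test level is set at 5%, one-sided.
- **Statistical Analyses** opens with: "The 1-sided chi-square 95% CI will be calculated to estimate the lower bound of iCC completion and trial retention rates". The next sentence sets acceptability: "We will consider participation in iCC acceptable if more than 50% of the participants completed at least 11 out of 21 intervention modules". The one after calls the trial feasible if week-12 attrition stays short of 50%.
- **Abstract, Methods** words acceptability with a non-strict inequality: "We will consider participation in iCC acceptable if ≥50% of the participants complete at least 11 out of 21 intervention modules". Its attrition criterion matches Statistical Analyses.
- **Study Strengths and Challenges** words feasibility the other way round: "To consider the trial feasible, at least 50% of participants must complete all study assessments at week 12".
- **Primary Outcomes** fixes the denominator as all randomised participants. It does not say whether retention is judged pooled or in each arm.

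**The concern.** The sample size is justified by a test with a null value, a level and a power. The criteria that decide acceptability and feasibility are stated as an observed proportion set against that same null value. A result just above 50% meets such a criterion but does not reject the null. Followed literally, the plan can call the app acceptable or the trial feasible on data that its own sizing test would treat as inconclusive.

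Completion and retention are the two primary outcomes, so this affects the trial's main conclusion. The boundary is also inconsistent. A completion rate of exactly 50% passes under the Abstract and fails under Statistical Analyses. A retention rate of exactly 50% passes under Study Strengths and Challenges and fails under the Abstract and Statistical Analyses.

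**Working it through.** **1. Reproduce the plan's figure.** Inputs from Sample Size: null 0.50, alternative 0.70, one-sided 5% (z = 1.645), 80% power (z = 0.842), normal approximation with binomial standard error.

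n = (1.645 + 0.842)² × 0.7 × 0.3 / 0.2² = 32.46, so 33 per arm. Then 2 × 33 / 0.7 = 94.3, which the plan gives as 94 and rounds to about 100. The sample size reproduces.

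**2. Numbers used below.** With 1:1 allocation, about 100 gives 50 per arm and 94 gives 47 per arm. The final number is not fixed, so both are shown. Completion uses the iCC arm. Pooled retention uses both arms; retention judged per arm would follow the n=50 or n=47 column.

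**3. Chance that the Statistical Analyses rule (observed rate above 50%) is met.** Exact binomial, P(X ≥ r | n, p), with r the smallest count above n/2:

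| True rate | n=50, r=26 | n=47, r=24 | n=100, r=51 | n=94, r=48 |
|---|---|---|---|---|
| 50% | 44.4% | 50.0% | 46.0% | 45.9% |
| 48% | 33.5% | 39.1% | 30.8% | 31.1% |
| 45% | 19.7% | 24.5% | 13.5% | 14.1% |
| 40% | 5.7% | 8.2% | 1.7% | 1.9% |

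The first row compares with the 5% used for sizing.

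**4. Effect of the boundary wording.** If exactly 50% passes, the chance at a true 50% becomes 55.6% (n=50) or 54.0% (n=100). The differences, 55.6 − 44.4 = 11.2 points and 54.0 − 46.0 = 8.0 points, are the probabilities of landing exactly on the boundary. With n=47 the wording makes no difference, because 50% cannot be observed.

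**5. An example of conflict.** At 26/50 (52%) the stated rule is met. The Wald lower limit is 0.52 − 1.645 × √(0.52 × 0.48 / 50) = 0.52 − 0.116 = 0.40, so the null of 50% is not rejected. Counts from 26 to 30 out of 50 (to 31 with an exact interval) meet the stated rule without rejecting the null.

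**6. What the rule would be if the bound decided.** Smallest count whose one-sided 95% lower limit exceeds 50%, with the error at a true 50% and the power at 70%:

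| n | Interval | Pass mark | Error | Power |
|---|---|---|---|---|
| 50 | exact | 32 (64%) | 3.3% | 85.9% |
| 50 | Wald or Wilson | 31 (62%) | 6.0% | 91.5% |
| 47 | exact or Wilson | 30 (64%) | 4.0% | 86.0% |
| 47 | Wald | 29 (62%) | 7.2% | 91.7% |
| 100 | any of the three | 59 (59%) | 4.4% | 99.3% |
| 94 | exact | 56 (60%) | 4.0% | 98.8% |
| 94 | Wald or Wilson | 55 (59%) | 6.1% | 99.3% |

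**The case against.** The best defence is that the bound is there. The sentence just before the criterion plans it, Sample Size speaks of a confidence-interval approach, and a one-sided lower bound has little use other than comparison with a threshold. A condensed article may leave the link to a fuller document. This stands in part: it would be wrong to infer that the plan ignores uncertainty, and the reported bound would let a reader see whether 50% is excluded. But the criteria appear in three sections, each time as an observed proportion, and none mentions the bound. That is the rule as stated, not only a missing detail.

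A reader might also infer that a failing app or trial would pass nearly half the time. The figures do not support that in general: 44% to 50% applies only at a true rate of exactly 50%, the least favourable point of the null, and the chance falls quickly below it.

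Nor do the documents make these criteria a formal gate to a larger trial. The Abstract's conclusion has only a loose condition of feasibility, and the closing Conclusions speak of informing adaptation and design.

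Observed-rate thresholds are a legitimate choice for a pilot. They are open to criticism here because this plan also set a null, a level and a power and justified its size by them.

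Finally, the boundary conflict is small. At the expected 70%, exactly 25/50 has a probability of about 0.1%.

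**Conclusion.** The point holds as a mismatch between the sizing test and the stated decision rule. The sample size itself is right. As worded, the criteria do not have the 5% error rate that justified about 100 participants: at a true 50% they are met 44% of the time with n=50, 50% with n=47, and 46% with n=100 or n=94. At a true 45% the figures are 20% (n=50) and 13% (n=100); at 40% they are 6% and 2%. These figures assume that the criteria are applied literally to the observed proportion among all randomised, and that retention is pooled where n is 100 or 94.

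The inconsistent boundary is a separate, lesser fault that needs no assumption about intent. It would also be a mistake to say that the sizing already presumes a 64% bar at n=50: the plan's normal-approximation method corresponds to 31/50 (62%), and 64% is the exact-interval mark.

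**What to change.** Use one rule in the Abstract, Statistical Analyses and Study Strengths and Challenges: iCC is acceptable, and the trial feasible, only if the lower limit of the one-sided 95% confidence interval for the rate among all randomised exceeds 50%. Remove the competing inequalities and report the observed rate as descriptive.

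Three details need settling with it:

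- **Interval.** Name one method. The exact interval keeps the error at or below 5%; Wald or Wilson gives about 6% at n=50.
- **Retention.** State whether it is judged pooled or per arm.
- **Pass mark.** Derive it from the number actually randomised. With the exact interval, for illustration, it is 32/50 or 30/47 for completion and 59/100 or 56/94 for pooled retention.

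The change is wording only and needs no more participants. Its cost is a stricter bar: about 64% observed completion in place of 52% (26/50). At the assumed true rate of 70%, power remains about 86% for completion and 99% for pooled retention, above the planned 80%. If the investigators prefer an observed-rate criterion, they should say that the 5% level does not apply to the decision and give the pass probabilities above.
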